### Outcome measures

3.9

The primary outcome measure will be the change from baseline to the treatment completion in the total MADRS score (0–6, normal or absence of symptoms; 7–19, mild depression; 20–34, moderate depression; >34, severe depression; Cunningham, Wernroth, Knorring, Berglund, & Ekselius, 2011; Herrmann, Black, Lawrence, Szekely, & Szalai, 1998; Muller‐Thomsen, Arlt, Mann, Mass, & Ganzer, 2005; Williams & Kobak, 2008). The MADRS will be used to assess the effects of ketamine in the three groups, specifically with the following 10 items, which are used widely for the measurement of depression severity: (a) apparent sadness, (b) reported sadness, (c) inner tension, (d) reduced sleep, (e) reduced appetite, (f) concentration difficulty, (g) lassitude, (h) inability to feel, (i) pessimistic thoughts, and (j) suicidal thoughts (Cunningham et al., 2011; Herrmann et al., 1998; Muller‐Thomsen et al., 2005; Williams & Kobak, 2008).

Patients will undergo objective cognitive testing at baseline and upon treatment completion. The Montreal Cognitive Assessment will serve as the primary cognitive measure (Nasreddine et al., 2005). The North American Adult Reading Test‐35 (Uttl, 2002) will be used to estimate intellectual function. The revised Hopkins Verbal Learning Test, Controlled Oral Word Association Test, and Stroop Color and Word Test will also be administered at baseline and at the end of treatment. Percentages of SV2A‐specific binding for synapse measurement on PET images will be calculated and compared between the two ketamine groups, and between baseline and completion of the 24‐week treatment period in each ketamine group.

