Working hypothesis 1: We hypothesize that ketamine will reverse chronic stress‐ and depression‐related deficits in synaptic connectivity in the PFC and hippocampus in patients with treatment‐resistant depression.Working hypothesis 2: We hypothesize that ketamine will recover chronic stress‐ and depression‐related volumetric abnormalities in the PFC and hippocampus in patients with treatment‐resistant depression.Working hypothesis 3: We hypothesize that ketamine treatment will markedly reverse deficits in synaptic density in the PFC and hippocampus compared with baseline, as measured by the percentage of SV2A‐specific binding on PET scans.Working hypothesis 4: We hypothesize that patients who receive ketamine at night will show better synapse restoration in the PFC and hippocampus than will those who receive ketamine during the day, as assessed by the percentage of SV2A‐specific binding on PET scans.

Specific aim #3: To identify and establish objective markers for the assessment of ketamine infusion therapy for treatment‐resistant depression using brain imaging studies.
Working hypothesis 1: We hypothesize that brain MRI studies of patients with treatment‐resistant depression will reveal the interaction of ketamine with its target sites in the brain, which could be linked to the drug's pharmacological effects and used for objective evaluation of the efficacy of ketamine.Working hypothesis 2: We hypothesize that in vivo synapse assessment using ^11^C‐UCB‐J‐PET imaging will enable the direct measurement of synaptic density as a potential new objective marker or outcome measure of the efficacy of ketamine.Working hypothesis 3: We hypothesize that MRI‐ and PET‐observed alterations will be linked, enabling the establishment of an “MRI–PET bridge” with tremendous potential as more useful approach in the next 10 years.

This study is innovative and highly significant within the field. Completion of the proposed research is expected to (a) shed new light on the mechanisms underlying ketamine's rapid and sustained antidepressant actions in patients with treatment‐resistant depression, (b) offer a more efficacious approach for ketamine infusion therapy for treatment‐resistant depression, and (c) provide suggestions for objective markers or measures for evaluation of the efficacy of ketamine for treatment‐resistant depression, or other clinical trials of therapies targeting synapse restoration.

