### PET imaging and analysis

3.6

For PET imaging, 40 patients will be randomly selected from the daytime and nighttime ketamine administration groups (20 per group) to undergo PET scans using the ^11^C‐UCB‐J PET ligand at baseline and upon completion of the 24‐week treatment period. This subset of patients will be included in consideration of the difficulties involved in brain PET, including poor patient compliance and high cost (Rausch et al., 2017; Thompson et al., 2016). In brief, PET imaging will be performed using a high‐resolution research tomography (GE Health Care) with a reconstructed image resolution of nearly 3 mm, as described previously (Finnema et al., 2018; Nabulsi et al., 2016). These patients will also undergo T1‐weighted MRI imaging in a 3‐T whole‐body scanner (GE HealthCare) at the same timepoints for coregistration with the PET images.

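### The PET hypothesis about ketamine overall has only a per-arm before-after comparison of 20 pairs each, with no rule for combining the two results

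*Protocol article*

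**What the plan says.** Section 2, Specific aim #2, working hypothesis 3 states that "ketamine treatment will markedly reverse deficits in synaptic density in the PFC and hippocampus compared with baseline", measured as the percentage of SV2A-specific binding on PET. It does not mention the hour of dosing. Working hypothesis 4 takes up timing separately: "patients who receive ketamine at night will show better synapse restoration in the PFC and hippocampus than will those who receive ketamine during the day".

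Section 3.6 sets the sample: "40 patients will be randomly selected from the daytime and nighttime ketamine administration groups (20 per group) to undergo PET scans", once at baseline and once when the 24 weeks of treatment end. The size is explained by patient compliance and cost; no power argument is given.

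Section 3.9 names two uses of the PET data. SV2A binding will be "compared between the two ketamine groups, and between baseline and completion of the" 24-"week treatment period in each ketamine group". Section 3.11 gives the general threshold of p < .05 and no model for PET.

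**The concern.** Hypothesis 3 asks one question: does binding change from baseline under ketamine? Forty scan pairs bear on it. The stated before-after comparison gives two answers from 20 pairs each, and the article does not say how they combine. If both arms must be significant, a real change will often be missed. If one arm is enough, a false-positive result becomes more likely.

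PET is the trial's direct measure of synaptic density, and Aim 3 proposes it as an objective marker of ketamine's efficacy. The subset is small for practical reasons, so the available pairs should be put to full use on the question they were collected for.

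**Working it through.** **Inputs from the article.** 20 daytime and 20 nighttime ketamine patients, one scan pair each (section 3.6); significance level 0.05 (section 3.11); 15% dropout, stated for the main trial only (section 3.8).

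**Assumptions.** Two-sided paired t test; one brain region at a time; the two arms independent. Neither the mean change in SV2A binding nor its SD is given, so I write d for the mean change divided by the SD of the change, take it as equal in both arms, and show a range. The article states no PET power figure, so there is none to reproduce.

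**Formula.** With n pairs, the test statistic is noncentral t with noncentrality d × √n. Power is the probability that it falls beyond the critical value.
- One arm: n = 20, 19 df, critical value 2.09. At d = 0.5 the noncentrality is 0.5 × √20 = 2.24, and power p = 56%.
- Both arms significant: p² = 0.5645² = 32%.
- Either arm significant: 1 − (1 − p)² = 1 − 0.4355² = 81%.
- All 40 pairs with arm in the model: 38 df, critical value 2.02. The noncentrality is 0.5 × √40 = 3.16, and power is 87%.

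| d (assumed) | One arm, 20 pairs | Both arms | Either arm | 40 pairs combined |
|---|---|---|---|---|
| 0.3 | 25% | 6% | 43% | 46% |
| 0.4 | 40% | 16% | 64% | 69% |
| 0.5 | 56% | 32% | 81% | 87% |
| 0.6 | 72% | 52% | 92% | 96% |

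**Change detectable with 80% power.** 0.66 SD with 20 pairs; 0.45 SD with 40.

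**With 15% loss** (20 × 0.85 = 17 per arm, 34 in all) at d = 0.5: 49% in one arm, 24% for both, 74% for either, 81% combined. The detectable change is 0.72 SD with 17 pairs and 0.50 SD with 34.

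**Error rate of an either-arm rule.** Counting a significant change in either direction, 1 − 0.95² = 9.75% against 5%. Counting only a false increase, which is what the hypothesis predicts, 1 − 0.975² = 4.94% against 2.5%. If each arm is tested at 0.025 to restore control, either-arm power at d = 0.5 falls to 69%.

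**Unequal arms.** With d = 0.3 in one arm and 0.7 in the other (mean 0.5), the arm-adjusted combined test still has 87% power. Both arms succeed in 0.247 × 0.844 = 21% of trials. At least one succeeds in 1 − 0.753 × 0.156 = 88%, at the inflated error rate.

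**The case against.** The article is a condensed account, and a fuller plan may contain a combined test. Section 3.9 says only that binding will be compared, without naming a test, so a group-by-time model with a time effect over all 40 patients is not excluded. Reporting by arm is also natural in a trial built on the idea that day and night dosing differ. This is a substudy of a self-described pilot, and the primary outcome is MADRS.

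Much of this stands. It limits the point to the fit between what is stated and what is hypothesised. But the article does specify the before-after comparison, and specifies it by group; the point does not rest on silence alone. The contrast with section 3.11 is telling: for MADRS it names ketamine versus placebo apart from day versus night, whereas PET has no comparison for ketamine overall.

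A reader might infer three stronger things that the article does not support.
- **Half the PET data are discarded.** They are not. All 40 pairs are analysed, 20 in each comparison.
- **Success in either arm counts as proof.** No success rule is stated. The either-arm and both-arms figures show what each possible rule would cost. Against an uncorrected either-arm rule the gain in power is modest (81% to 87% at 0.5 SD), and the rest of the benefit is control of the error rate.
- **Timing will be judged from one arm being significant and the other not.** Section 3.9 already lists the direct comparison of the two ketamine groups, which is the right test of timing.

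**Conclusion.** The concern holds in a limited form. Hypothesis 3 is about ketamine overall, the only stated before-after PET comparison is per arm, and no rule joins the two results. At an assumed change of 0.5 SD, equal in both arms, one arm-adjusted test on 40 pairs has 87% power. The alternatives are 32% under a both-arms rule, or 81% under an either-arm rule that nearly doubles the false-positive rate. The detectable change improves from 0.66 to 0.45 SD. The power figures depend on the assumed effect; the advantage of the combined test over a single arm or a both-arms rule holds across the range shown.

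This is a free improvement to a secondary analysis and leaves the primary analysis untouched. It does not make the PET result causal: without placebo PET, neither the combined nor the per-arm change can separate ketamine from the passage of time or other influences.

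**What to change.** In section 3.9:
- Name the test of hypothesis 3 as the mean change in SV2A-specific binding from baseline to 24 weeks, averaged over the two arms, in all 40 PET patients, with arm as a factor in the model.
- Keep the between-group comparison as the test of hypothesis 4.
- Report the change within each arm with a confidence interval, as secondary.
- State that the combined change is an uncontrolled before-after estimate.

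The cost is a few sentences. No further scans or patients are needed, and no planned result is lost.

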### Side effects and safety

3.10

The occurrence of adverse events and side effects, including memory complaints reported by patients and recorded by physicians, will also be evaluated. Ketamine has been reported to be associated with neurocognitive impairments, manifesting mainly as memory recall problems (Murrough et al., 2013). Patients' neurocognitive function will also be assessed using a comprehensive battery including the estimated premorbid intelligence quotient (IQ), current IQ, and tests from the MATRICS Consensus Cognitive Battery, as described previously (Murrough et al., 2013). Data on patients' self‐reported memory complaints will be collected using the Squires Memory Complaint Questionnaire, Global Self‐Evaluation of Memory, and Patient‐Rated Inventory of Side Effects. Data on physician‐reported adverse events and side effects will be collected using the Brief Psychiatric Rating Scale psychotic subscale and the Clinician‐Administered Dissociative State Scale.

Upon the development of serous medical complications, including but not limited to suicidal ideation, cardiovascular toxicity, and infusion‐related side effects, the participants will be advised to withdraw from the study and will receive prompt care in the emergency room.

### Data handling and statistical methods

3.11

Baseline demographic information and clinical characteristics of the enrolled patients will be compared among groups using one‐way analysis of variance (ANOVA) or the Kruskal–Wallis *H* test, as appropriate, for continuous variables, and the chi‐squared test or Fisher's exact test, as appropriate, for nominal variables. The effects of different treatments on MADRS scores will be examined using one‐way ANOVA, followed by post hoc testing of ketamine versus placebo and daytime versus nighttime ketamine administration. A multiple linear regression analysis of estimated conditional treatment effects will be conducted for effect measure modification.

The IBM SPSS version 20.0 software (IBM Corp.) will be utilized for statistical analyses. *p* values <.05 will be taken to indicate significant differences between groups. The statistical software and methods used may change if newer software becomes available.

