### Human subjects

3.1

Potential patients will be enrolled from the Tianjin Mental Health Center affiliated with Tianjin Medical University in Tianjin, a coastal metropolis in northern China with approximately 13,000,000 residents. Eligible patients will (a) be aged 18–65 years to minimize potential older age‐related confounding effects, such as AD and cognitive impairment; (b) meet the Diagnostic and Statistical Manual of Mental Disorders fifth edition criteria for recurrent MDD without psychotic features, which will be confirmed using the Mini International Neuropsychiatric Interview (Sheehan et al., 1998; Singh et al., 2016); (c) have inadequate responses to at least two antidepressant medications, with at least one antidepressant failure to treat current depressive episodes, as evaluated by medical histories, the Massachusetts General Hospital Antidepressant Response Questionnaire, and Montgomery‐Asberg Depression Rating Scale (MADRS) score ≥21 at baseline (Chandler, Iosifescu, Pollack, Targum, & Fava, 2010; Ng et al., 2019; Singh et al., 2016); (d) be willing to participate and fully cooperate in this study; and (e) provide written informed consent prior to study participation. Patients with the following conditions will be considered to be ineligible and will be excluded from the study: (a) severe systemic disease; (b) epilepsy, claustrophobia, primary obsessive–compulsive disorder, anorexia nervosa, bulimia nervosa, or posttraumatic stress disorder; (c) medical history or current diagnosis of a psychotic disorder; (d) medical history or current diagnosis of mental retardation, bipolar disorder, mood disorder with postpartum onset, borderline personality disorder, or somatoform disorder; (e) hypertension or vascular disease, including aneurysm, vascular malformation, thrombosis, and neoplasm; (f) unfitness for MRI, including the presence of a magnetic implant; (g) unfitness for PET, including allergy to PET tracers; (h) substance abuse; (i) use of medicine for a sleep disorder; (j) medical history of nonresponsiveness of depressive symptoms to ketamine; (k) clinically significant suicidal or homicidal ideation or imminent risk of harm; and (l) current pregnancy or breastfeeding status. Independent World‐Class Services for Drug Development and Clinical Trial Success (SAFER) raters from Massachusetts General Hospital will be used to verify that all randomized patients meet the SAFER criteria, have treatment‐resistant MDD based on the Antidepressant Treatment Response Questionnaire, and manifest the required depression severity.

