### Randomization and treatment

3.2

R/S‐ketamine hydrochloride, sold under the brand name Ketalar (Pfizer Pharmaceuticals), will be used as the study drug. A total of 600 adult patients with treatment‐resistant depression will be enrolled in this study. Randomization and stratification of the study patients will be carried out using the Randomization in Treatment Arms software (Evident). The patients will be assigned to the following three groups (200 per group): placebo, daytime ketamine administration, and nighttime ketamine administration. Patients in the ketamine groups will be given ketamine infusions at a dose of 0.5 mg/kg (R/S‐ketamine hydrochloride diluted in saline, administered slowly by i.v. pump for >40 min) in the morning and at night, respectively (Berman et al., 2000; Zarate et al., 2006); patients in the placebo group will receive matching saline infusions (Figure 1). These patients will receive two infusions per week for 24 weeks (Singh et al., 2016). Treatments will be administered in private rooms at the Mental Health Teaching Hospital affiliated with Tianjin Medical University.

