### Limitations of this study protocol

4.2

Despite the obvious strengths of this study, some potential limitations of our study protocol should be noted. First, we recognize that this entire pilot study will be conducted at a single center and that selection bias may be a weakness. In addition, our hospital‐based enrollment method could affect our findings. Second, although the sample size was calculated to generate sufficient power for the assessment of differences in intervention efficacy among study groups, it may not be large enough to enable analysis of subgroups, such as those defined by sex and genetic variants. Third, although we do not anticipate this to be the case, it is possible that differences in certain patient characteristics could affect the outcomes. Another weakness of this protocol could be that we will not be able to stratify randomization by sex.

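### The primary MADRS analysis is a one-way ANOVA without adjustment for baseline MADRS or the randomisation strata, and section 3.11 lets newer software be a reason to change the method

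*Protocol article*

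**What the plan says.** Section 3.9 defines the endpoint: "The primary outcome measure will be the change from baseline to the treatment completion in the total MADRS score". Section 3.11 gives its analysis: "The effects of different treatments on MADRS scores will be examined using one‐way ANOVA", followed by post hoc tests of ketamine against placebo and of daytime against nighttime dosing.

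Section 3.11 contains one multivariable model, for a different purpose: "A multiple linear regression analysis of estimated conditional treatment effects will be conducted for effect measure modification". Its covariates are not named.

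Section 3.2 says that the randomisation is stratified, without naming the factors: "Randomization and stratification of the study patients will be carried out using the Randomization in Treatment Arms software". Section 3.1 makes a baseline rating a condition of entry: "Montgomery‐Asberg Depression Rating Scale (MADRS) score ≥21 at baseline".

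Section 4.2 lists as limitations that "it is possible that differences in certain patient characteristics could affect the outcomes" and that "we will not be able to stratify randomization by sex".

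Section 3.11 ends: "The statistical software and methods used may change if newer software becomes available".

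**The concern.** The named method cannot use information that the design has already paid for. Baseline MADRS is measured in everyone and the randomisation is stratified, yet a one-way ANOVA has no place for either. Section 4.2 accepts that patient characteristics may affect outcome, but no adjustment of the main comparison follows.

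Three things are at stake.
- **Precision.** Aim 1 compares two active groups given the same drug at different times of day. Residual variance that could have been removed widens the interval for that contrast.
- **Calibration.** After stratified randomisation, an analysis that leaves out prognostic strata reports standard errors that are too wide.
- **Clarity of the endpoint.** Section 3.9 speaks of change and section 3.11 of MADRS scores. Without baseline in the model, these are two different analyses with different variances.

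Separately, a sentence that lets methods change when software is updated weakens the prespecification of the primary test. New software is not a statistical reason to replace it.

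**Working it through.** The document gives no figure for this point that could be reproduced: no MADRS SD, correlation or effect size is stated. The check is therefore a comparison of variances over assumed ranges.

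**Inputs.** From the document: the primary outcome is change in MADRS (3.9); the model is treatment only (3.11); the entry cut is MADRS 21 or above (3.1); there are 200 patients per group (3.2) and 15% dropout (3.8). Assumed: r between 0.2 and 0.5, and either equal SDs at baseline (s0) and week 24 (s1), or s0 equal to half of s1 because the entry cut narrows the baseline range.

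**Formulas.**
- Variance of a change score: s0² + s1² − 2·r·s0·s1
- ANCOVA residual variance: s1²·(1 − r²)
- Variance of the week-24 score: s1²

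**Equal SDs.** The ratio of ANCOVA to change score is (1 − r²)/[2(1 − r)] = (1 + r)/2.

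**Halved baseline SD,** for example s0 = 5 and s1 = 10. The change-score variance is 125 − 100r, and the ANCOVA variance is 100(1 − r²).
- r = 0.2: 96/105 = 0.91
- r = 0.3: 91/95 = 0.96
- r = 0.5: 75/75 = 1.00

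**Against an ANOVA of week-24 scores.** The ratio is 1 − r².

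| Assumed r | vs change, equal SDs | vs change, s0 = s1/2 | vs week-24 score |
|---|---|---|---|
| 0.2 | 0.60 | 0.91 | 0.96 |
| 0.3 | 0.65 | 0.96 | 0.91 |
| 0.5 | 0.75 | 1.00 | 0.75 |

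**In terms of power.** With equal SDs, where a change-score ANOVA has 80% power for a pairwise contrast, ANCOVA has about 93.5% at r = 0.3 and about 90% at r = 0.5. This is the favourable case. With the halved baseline SD the gain is small, and at r = 0.5 it is nil.

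**Unmodelled strata.** If the strata explain a share R² of the outcome variance, the true standard error is about √(1 − R²) of the reported one. The actual two-sided level of a nominal 0.05 test is then 2·[1 − Φ(1.96/√(1 − R²))]. For assumed R² of 5%, 10% and 20% this gives 0.044, 0.039 and 0.028. The factors are not named, so the document does not show which value applies.

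**Chance imbalance.** With 200 × 0.85 = 170 completers per group, the baseline difference between two groups has an SD of √(2/170) = 0.108 baseline SDs. With equal SDs, an imbalance of that size shifts an unadjusted change-score contrast by (1 − r) × 0.108: 0.076 SD at r = 0.3 and 0.054 SD at r = 0.5. ANCOVA removes this.

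**Change or score.** With baseline as a covariate, modelling change or the week-24 score gives the same treatment estimate and standard error. Only the baseline coefficient differs, by 1.

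**The case against.** The strongest reply is that this is a preference about efficiency, not an error. The unadjusted ANOVA is unbiased under randomisation, and leaving out prognostic strata makes the test conservative. The gain is uncertain: r is assumed, a narrow baseline range can remove most of it, and the loss from the strata cannot be sized while the factors are unnamed. ANCOVA is also not guaranteed to win. With three groups and unequal slopes, a common-slope model can be less precise for a pairwise contrast. Finally, an article condenses the full protocol, and covariates are commonly left to an analysis plan.

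Most of this stands, and it limits the point to a recommendation. The last argument stands only in part: section 3.11 names a specific unadjusted method and reserves its regression for effect modification, so the choice is stated and not merely left open.

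A reader might also infer more than the document supports:
- **That baseline is ignored.** It is not. A change score uses baseline by subtraction; what is missing is adjustment for it.
- **That leaving out sex contradicts the randomisation.** Sex is not a stratification factor, so there is no mismatch. It is at most an unused covariate, and section 4.2 discloses the limitation honestly.
- **That the day-night difference is expected to be small.** No passage gives its size.
- **That the last sentence of 3.11 gives free discretion.** It is conditional on newer software.

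**Conclusion.** The point holds as a worthwhile improvement to a stated analysis choice. The one-way ANOVA is valid. It leaves precision unused and is conservative to the extent that the strata are prognostic.

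For r of 0.2 to 0.5, the size ranges from a 25-40% reduction in residual variance (equal SDs, change score) to 0-9% (baseline SD halved). Against week-24 scores the reduction is 4-25%. All of these rest on assumed correlations and SDs. The cost of leaving out the strata is real in direction but unknown in size.

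The clause on changing methods is a genuine but secondary defect. Any concern about protecting the 0.05 level attaches to that clause and not to the unadjusted ANOVA, which does not inflate the error rate for the reasons discussed here.

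**What to change.** In section 3.11, replace the ANOVA sentence with wording such as: *Change from baseline to week 24 in total MADRS will be analysed by ANCOVA with treatment group, baseline MADRS and the randomisation stratification factors as terms. Ketamine versus placebo and daytime versus nighttime ketamine will be estimated as prespecified contrasts.* Both comparisons are already in 3.11. Sex may be added as a prespecified covariate. Naming the outcome as change also aligns 3.11 with 3.9.

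In the last sentence of 3.11, delete the words *and methods*, and state that a change of method is allowed only if documented before unblinding.

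Leave the sex limitation in section 4.2 as it stands. It remains true, and putting sex in the model does not alter how patients were randomised.

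The cost is a change of wording and one covariate plus a few terms in the model. The stratification factors must be known to the analyst; the article does not name them, so their availability cannot be checked here. No change to the randomisation system is needed.
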